#### Intervention outcomes

All outcomes at individual level are assessed at baseline, directly after the end of the intervention and again after 6 months. The primary intervention outcome is physical activity, which is assessed by pedometry (Yamax 200). The Yamax 200 pedometer has shown high agreement with accelerometer-measured physical activity [24,25] and is recommended for research purposes [26]. A previous study on adults with ID has shown that three days of measurement is needed to predict the usual weekly number of steps per day [27]. The participants receive the pedometer and, together with staff in residences, get practical training as well as verbal and easy to read instructions from the research staff on how to wear it (attached to a belt or lining around the waist, vertically in line with the knee), how to record the number of steps per day and how to reset the pedometer for the next day of measurement. The participants are asked to wear the pedometer for seven consecutive days, but for the analysis we will include participants that have at least three days of measurements. The outcome measure is average total steps per day as an indicator of total physical activity.

Dietary quality, which is a secondary outcome, is assessed by personal digital photography, a method which has been developed and validated for this project and will be published. Each participant, as well as residence staff, is instructed on how to use the camera (Canon PowerShot A480) and receives practical training in taking pictures. Photos are taken by the participants themselves of all foods and beverages consumed during three days and staff is encouraged to remind participants to take photos or to assist, if necessary. Outcome measures are: 1) Intake occasions of indicator foods and beverages (fruit and berries, vegetables, low nutrient density foods and beverages, and beverages excluding water); 2) Meal quality assessed in comparison to food-based dietary guidelines visualised as the plate model [28] and; 3) Dietary diversity covering nine core food groups.

It is important to assess the effects of health promotion efforts on the quality of life, which may improve or worsen as a consequence of the intervention. Quality of life, a secondary outcome, among people with ID is assessed by a multi-factorial quality of life scale which has been developed within this project, because no suitable scale could be identified from the literature. We selected questions from various quality of life questionnaires and reconstructed and pretested them. The questions include information about quality of life within six domains (home, food and meals, leisure, family and friends, physical health and mental health) and have three response alternatives; good, average or bad. The questions in the scale are read to participants in the form of a structured interview by the research team. Residence staff is asked not to be present during the interview, only if they think it is necessary for the sake of the respondent. The scale will be tested for its psychometric properties in participants in the study according to Kline el al. [29].

Height, weight and waist circumference are secondary outcomes and are measured by the research staff, at the residence. Height is measured to the nearest cm in a standardized way using SECA stadiometer (214). Weight is measured using a digital scale (SECA Robusta 813) to the nearest 0.5 kg with light clothing, and the body mass index (BMI kg/m^2^) is calculated. Waist circumference is measured to the nearest cm at the midpoint between the lowest rib and the iliac crest at the end of expiration. Participants answer questions regarding age, country of birth, occupation, family and physical functional limitation. If necessary, the staff gives supplementary information.

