### Planning of the intervention and development of materials

When planning this intervention we employed the step-by-step approach as described by Fraser et al. [20]. In step 1 we have specified the problem and defined our problem theory. Based on previous research and practitioner's experience, we have identified poor dietary habits, low physical activity and weight disturbances among adults with ID. In addition, the low educational level of staff working in community residences in general has been identified as a barrier to healthy lifestyles among the target group. Our goal with the intervention is therefore to improve diet and physical activity of the residents as well as knowledge and skills of both residents and the staff. The intervention is based on social cognitive theory (SCT). This theory explains behaviour in terms of a triadic, dynamic, and reciprocal model in which behaviour, personal factors, and environmental influences all interact [21]. According to this theory, we aim to improve health behaviours through both personal factors (knowledge, skills, preferences, self-efficacy) of residents as well as through improvements in their social and physical environment, which is very much dependent on knowledge, skills and work routines of the staff.

In step 2 of intervention planning, core components of the intervention are identified and programme materials are developed and pretested. "Fokus hälsa" (Focus health) is a newly developed material with ten themes for use by staff. It aims to increase the knowledge and skills of residence staff with regard to diet, physical activity and health and is based on the principles of peer education [22]. The themes were developed in discussions with managers of community residences and on the basis of their knowledge of the needs of the target group. The themes are: 1) Health and quality of life; 2) Autonomy and ethics; 3) National recommendations concerning diet and health and information in society; 4) Healthy dietary habits; 5) Physical activity for health; 6) Availability and accessibility; 7) Habits and attitudes; 8) Motivation and support for behavioral change; 9) Cooperation; and 10) How to sustain good work. Each theme includes an introductory text, which is read before the meeting, and at the end there are three suggested exercises: 1) Questions for discussion; 2) Identification of strengths and weaknesses in work routines; and 3) Making agreements about new and improved work routines.

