#### Health ambassadors

Ambassadors for various issues are common among the staff in community residences and we wanted to build on this practice. Therefore, in every participating community residence a health ambassador is appointed among staff members. The task of the health ambassador is to provide health information to colleagues and inspire them and to plan and organise health promoting activities for residents. The health ambassador receives coaching by the research team on issues regarding diet, physical activity and health and gets the possibility to exchange knowledge and experiences during network meetings with health ambassadors from the other residences. Network meetings are arranged four times during the intervention. The first meeting is an introductory meeting and following meetings focus on themes chosen by the ambassadors.

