#### Study circle for staff

The aim of the study circle is to increase the knowledge and skills of staff in the area of health promotion in order to empower them to improve work routines and the social and physical environment of residents. Normally, staff in community residences meet once every second or fourth week. We decided that these meetings would be a good opportunity for the staff to conduct this study circle using the study material "Fokus Hälsa" (Focus Health). All the staff in every community residence, including the health ambassador, comes together to discuss health issues, based on the principles of peer education [22]. A discussion leader is appointed and the group discusses and does the exercises according to the instructions in the material.

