### Evaluation design

Step 3 in intervention research [20] constitutes the evaluation of the intervention with regard to individual outcomes and setting level impacts. Because we are targeting both residents and staff the study is designed as a cluster-randomised trial. After baseline measurements are completed, residences are randomised to an intervention group and to a waiting list-control group by a computer-generated list of random numbers done by the statistician, and concealed from the research staff, which enrols the participants. Evaluation is done by mixed methods, using both quantitative and qualitative methods.

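### Residence staff, who know their arm at follow-up, may choose to attend the quality-of-life interview, so their presence could differ by arm and bias this secondary self-report outcome

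*Protocol article*

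**What the plan says.** Quality of life is a secondary outcome, measured with a project-specific scale of six domains and three response levels (Intervention outcomes). On how it is administered, the protocol says: "The questions in the scale are read to participants in the form of a structured interview by the research team". On who else may be in the room: "Residence staff is asked not to be present during the interview, only if they think it is necessary for the sake of the respondent". Staying away is thus the default and attending is the exception. The exception is decided by staff, on their own view of the resident's need, and no criterion is given.

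The same section gives the timing: "All outcomes at individual level are assessed at baseline, directly after the end of the intervention and again after 6 months". Evaluation design gives the order of events: "After baseline measurements are completed, residences are randomised to an intervention group and to a waiting list-control group".

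Staff in intervention residences are a target of the intervention. Study circle for staff says: "The aim of the study circle is to increase the knowledge and skills of staff in the area of health promotion", and "All the staff in every community residence, including the health ambassador, comes together to discuss health issues". One of its ten themes is "2) Autonomy and ethics" (Planning of the intervention and development of materials). The only blinding stated is that of the statistician (Data analysis).

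**The concern.** Residents may answer differently about their home, meals or leisure when someone who works there is listening. Asking staff to stay away suggests that the authors prefer interviews without them. If the exception were used equally in both arms, it would add noise but no bias. The difficulty is that the people who decide on it know their allocation at both follow-ups, and in one arm they have been through a programme meant to change how they support residents. Their view of when a resident needs them could shift in that arm and not in the waiting-list arm.

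A difference arising this way is created at data collection. A blinded statistician cannot remove it. Adjusting for the baseline score cannot either, because that score was taken before the arms could diverge. The stake is the reading of one secondary outcome, which the protocol includes because it could move in either direction under the intervention. The primary outcome, pedometer steps, is not affected by this rule.

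**Working it through.** **Step 1. Put the provisions in order.**

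| Interview | Relation to randomisation | Staff deciding on the exception |
|---|---|---|
| Baseline | Before | Cannot know the arm |
| End of intervention | After | Know the arm; intervention staff have been offered the study circle |
| 6 months later | After | As above |

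The presence rule is stated once and is not limited to baseline. That it also governs the follow-ups is an inference from this and from the three-visit schedule. Nothing in the article counters it. The interviewers are not a stated check on the staff's decision: they belong to the research team, and that team also works with intervention residences ("The health ambassador receives coaching by the research team on issues regarding diet, physical activity and health").

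**Step 2. The plan's own figures.** There is none for quality of life or for staff presence. The only sample-size figure is 32 residences for steps per day (Statistical power), used here only for the number per arm. Its inputs are mean 6621, SD 3366, a 25% increase, two-sided 5%, 80% power and cluster size 5.

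- Difference: 0.25 × 6621 = 1655.25 steps.
- Individuals per arm without clustering: 2 × [3366 × (1.960 + 0.842) / 1655.25]² = 64.9.
- With an assumed intracluster correlation (ICC; the article states none) of 0.05, the design effect is 1 + 4 × 0.05 = 1.2. Then 64.9 × 1.2 / 5 = 15.6, so 16 residences per arm and 32 in total, as stated.
- Residents per arm: 16 × 5 = 80.

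**Step 3. Illustrate the size.** All presence inputs below are assumptions.

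- Spurious difference b = (shift in score when staff are present, in SD) × (difference between arms in the share of interviews with staff present). This takes the shift to be the same in both arms.
- Standard error, carrying ICC 0.05 over to quality of life: √(2 × 1.2 / 80) = 0.173 SD.
- Rejection rate of a two-sided 5% test with no true effect: 1 − Φ(1.96 − b/SE) + Φ(−1.96 − b/SE).

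| Shift (SD) | Gap in presence | b (SD) | Rejection rate |
|---|---|---|---|
| any | 0 | 0 | 5% |
| 0.2 | 10 points | 0.02 | 5.2% |
| 0.5 | 20 points | 0.10 | 8.9% |
| 0.5 | 30 points | 0.15 | 13.9% |
| 0.8 | 50 points | 0.40 | 63.7% |

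For scale, the difference detectable with 80% power at this size is (1.960 + 0.842) × 0.173 = 0.49 SD, so the 0.10 SD case is about a fifth of it. The last row is an extreme. The sign of b follows the sign of the gap and of the shift, and the documents fix neither.

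**The case against.** The strongest reply is that the protocol already has the right safeguard. Staff are asked to stay out, and the exception protects residents who need support. No passage says that the intervention changes attendance at interviews, so the mechanism is conjecture. On modest inputs the distortion is small against what the trial could detect. Recording of presence and model covariates are matters that an article commonly leaves to the full protocol, the interview manual or the analysis plan.

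Most of this stands, and it limits the point. The default is protective and should be kept. That the article does not mention recording, or a model term for presence, is not the finding. What the reply does not remove is the stated rule: the exception rests on the judgement of people who know the allocation and, in one arm, are themselves treated.

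A reader might infer more than the text supports in three ways:

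- **That staff have open discretion at every visit.** The text sets absence as the default, and its use at each visit is inferred.
- **That staff presence would rise in the intervention arm and hide a worsening of quality of life.** Nothing supports that direction. The study-circle theme on autonomy could as easily lower presence.
- **That intervention staff spend 12–15 months in the study circle.** That is the length of the whole intervention. Ten themes at meetings every second to fourth week come to 10 × 2 = 20 to 10 × 4 = 40 weeks, assuming one theme per meeting.

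**Conclusion.** The point holds as a risk to one secondary outcome. The stated rule allows staff presence at the two follow-up interviews to depend on allocation, and nothing in the article prevents it. The conclusion rests on two readings: that the rule applies at all three visits, and that presence can affect answers. The direction is unknown. The size cannot be derived from the documents, and the illustrations run from negligible (0.02 SD) to large (0.40 SD) according to the inputs assumed. Under the formula used, the bias is zero if presence is equal in both arms. It would be wrong to conclude that the quality-of-life comparison is biased. The supported conclusion is that it is left open to an avoidable bias that costs little to close.

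**What to change.** Keep absence of staff as the default and change how the exception works.

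1. At baseline, before randomisation, record for each resident whether a supporter is needed in the interview.
2. Use the same arrangement at both follow-ups. Allow a departure at the resident's request or for a genuine change in need, and record it with the reason.
3. Record staff presence at every interview and report it by arm and visit, so that readers can see whether the arms diverged.
4. Include the pre-randomisation arrangement as a covariate in the quality-of-life model. Do not adjust the main model for presence after randomisation, because the intervention may have influenced it.
5. Label any analysis restricted to interviews held under the same condition as exploratory, because that subset is selected after randomisation.

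The cost is one form field, a sentence or two in the interview instructions and one descriptive table. Staff lose a little flexibility. Support stays available to residents who need it, including those whose needs change. Departures can still differ by arm, but they will be visible.

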#### Impacts at setting level

Changes in health promotion work routines and healthy living opportunities in community residences are monitored by self-assessment by residence managers. We developed a questionnaire called Work routines for meals, physical activity and health (Additional file 1). It includes 26 items structured into 3 sections: General health promotion, food and meals, and physical activity. The questionnaire has undergone cognitive response testing but is not otherwise validated. The questionnaire is answered at baseline, after completed intervention and again at 6 months follows up in both intervention and control residences.

#### Fidelity criteria

Fidelity is defined by the extent to which a programme is implemented as intended, and the effectiveness of an intervention is related to fidelity [30]. Fidelity is assessed based on participation of residents and staff in the intervention activities. Fidelity is assessed by counting the number of times that residents and staff participate in health education and the study circle, respectively. Residents' participation is documented by the education leaders, staff participation is self-monitored and attendance at health ambassador's network meetings is documented by the research staff. A scoring system is developed with a 3-grade score, high, middle and low participation. Additional fidelity assessment is performed for the study circle for residence staff. A score is given to each residence based on the number of themes they have covered and to which extent they have made agreements about new and improved work routines.

#### Statistical power

Calculation of power is based on the assumption of an average 25% increase in physical activity, assessed as steps per day by pedometry. No Swedish data were available so we used data from Peterson et al [31] from the USA for adults with mild to moderate intellectual disabilities, who on average achieved 6621 ± 3366 steps per day. Calculations were performed with the "Sample size calculator for cluster randomized trials" [32]. The calculation was 2-sided, and power was set to 80%, the significance level to 5%, and cluster size to five individuals. The calculation shows that 32 community residences are needed to detect a significant change in physical activity of 25% between the intervention and control group.

#### Data analysis

Data analysis will be performed by the statistician who is blinded to the intervention group assignment. At individual level, parametric and non-parametric tests are used to compare groups at baseline, depending on the distributions of the quantitative variables. In order to account for clustering of the data, multilevel analysis is used to evaluate the effects of the intervention on relevant outcomes. Two levels are defined in the analysis: 1) individual and 2) residence. Linear and logistic regression models are used to study the effect on the outcome variables physical activity, intake occasions of indicator foods, meal quality, dietary diversity, body weight status, BMI and quality of life. Intervention outcome will be evaluated in relation to the intervention dose (fidelity score) but also to the intention to treat principle.

To evaluate the impact of the intervention on work routines and opportunities for a healthy diet and physical activity in community residences ordinal regression will be used for the data derived from the questionnaire Work routines for meals, physical activity and health (Additional file 1). Multinomial logistic regression might also be used if it is the categories and not the order of the categories per se that is of importance for the results. If the dependent variable can be adequately dichotomised, we will use Poisson regression with robust error variance (modified Poisson regression) to estimate risk ratios (relative risks).

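### Outcome analysis: adding each resident's baseline value to the two-level model, and stating how the three occasions are handled, is a free gain in precision

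*Protocol article*

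**What the plan says.** The protocol article, under Intervention outcomes, sets the measurement schedule: "All outcomes at individual level are assessed at baseline, directly after the end of the intervention and again after 6 months". For the primary outcome this yields one value per resident and occasion: "The outcome measure is average total steps per day as an indicator of total physical activity". Under Evaluation design, baseline comes first: "After baseline measurements are completed, residences are randomised to an intervention group".

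The Data analysis section gives the model and its purpose: "In order to account for clustering of the data, multilevel analysis is used to evaluate the effects of the intervention on relevant outcomes". It then fixes the hierarchy: "Two levels are defined in the analysis: 1) individual and 2) residence". Linear and logistic regression are named for the outcomes. The only stated use of baseline data is a comparison of the arms: "parametric and non-parametric tests are used to compare groups at baseline, depending on the distributions of the quantitative variables". The section names no baseline covariate, change score, time term or occasion level, and does not say which follow-up carries the primary effect.

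**The concern.** Three occasions per resident and a two-level model can be combined in more than one way, and the text does not say which is meant.

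- **Each follow-up is analysed on its own.** Two levels are then right. As written, though, nothing brings in the resident's own baseline value, which is likely to predict later steps and is collected before allocation.
- **Baseline and follow-up are stacked and the effect is read from an arm-by-time term.** Repeated values from one person are then correlated. If residence is the only random effect, that correlation goes into the residual and the standard error of the change contrast is wrong.

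At stake is the power of the primary comparison. The trial is sized at 80% power, and the Discussion says residences are not easy to recruit, so precision available at no cost is worth having.

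**Working it through.** **Inputs from the Statistical power section.** Mean and SD: "who on average achieved 6621 ± 3366 steps per day". Effect 25%, two-sided 5% level, 80% power, five residents per residence, 32 residences. Equal allocation is assumed: 16 residences and 80 residents per arm.

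**Assumed, because the article gives no figure.** ICC 0.05; correlation r between baseline and follow-up steps of 0.3 to 0.7.

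**1. The plan's own figure.**
- Effect: 0.25 × 6,621 = 1,655 steps.
- Residents per arm without clustering: 2 × [3,366 × (1.960 + 0.842) / 1,655]² = 64.9.
- Design effect at ICC 0.05: 1 + (5 − 1) × 0.05 = 1.2.
- 64.9 × 1.2 = 77.9 per arm; 77.9 / 5 = 15.6, rounded up to 16 residences per arm, 32 in all.

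The stated 32 is reproduced for an ICC from 0.04 to 0.058. An ICC of 0 gives 26 and 0.06 gives 34. This calculation uses follow-up values only, with no allowance for baseline.

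**2. Follow-up alone, two levels.**
- SE = 3,366 × √(2 × 1.2 / 80) = 583 steps.
- Power = Φ(1,655 / 583 − 1.96) = Φ(0.88) = 81%.

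**3. Same two-level model with baseline steps as covariate.** SE = 583 × √(1 − r²), taking the same r at resident and residence level.

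| r (assumed) | SE (steps) | Power |
|---|---|---|
| 0 (not used) | 583 | 81% |
| 0.3 | 556 | 85% |
| 0.5 | 505 | 91% |
| 0.7 | 416 | 98% |

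A simulation of 300 null trials (32 residences of five, ICC 0.05, r = 0.6) confirmed that both two-level models are valid. In SD units, follow-up alone had an empirical SD of 0.174, a mean model SE of 0.173 and 5.3% rejections. With the baseline covariate the figures were 0.134, 0.134 and 6.0%.

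**4. Baseline and one follow-up stacked, arm-by-time effect, residence the only random effect.** Take total variance as 1, the residence effect as constant over time, person variance p = r − 0.05 and occasion variance e = 1 − r.
- True SE of the contrast: 3,366 × √(4e / 80), because residence and person effects cancel in a within-person change.
- Within-residence degrees of freedom: 320 − 32 − 2 = 286. Of these, 128 (32 × 4) are between persons, with expected mean square e + 2p; the other 158 have e. The fitted residual variance is therefore about e + (256 / 286)p.
- Model SE: 3,366 × √(4 × [e + 0.895p] / 80).
- Type I error: 2 × [1 − Φ(1.96 × model SE / true SE)]. Power: Φ((1,655 − 1.96 × model SE) / true SE).

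| r (assumed) | True SE | Model SE | Type I error | Power |
|---|---|---|---|---|
| 0.3 | 630 | 723 | 2.4% | 65% |
| 0.5 | 532 | 715 | 0.8% | 68% |
| 0.7 | 412 | 707 | 0.1% | 74% |

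Simulated fits of this model (250 null trials) rejected 0.8% at r = 0.5 and 0.4% at r = 0.7. That is two trials and one trial, so only the order of magnitude counts.

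**5. Both follow-ups stacked for an average effect, residence the only random effect.** The standard error stays about right: empirical SD 0.164 against model SE 0.166 at r = 0.5, and 0.166 against 0.167 at r = 0.7, with 3.6% and 4.8% rejections. The residence term absorbs most of the person variance in the residence means.

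**The case against.** The strongest reply is that nothing in the article is wrong. With one value per resident in each model, two levels are the correct hierarchy, with or without a baseline covariate, and also for a change score. One of the two remedies below leaves the two-level sentence untouched. The article never says that occasions are stacked. If they were, the individual level it names could serve as the person term. Covariate lists are commonly left to the full protocol or analysis plan. The sample size is itself a follow-up-only calculation, so an unadjusted analysis delivers about the planned power.

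Most of this stands. Three stronger readings are tempting, and the documents support none of them:

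- **That the two-level sentence is an error.** It is correct for a single follow-up value per person.
- **That baseline is left out.** The article is silent on this. The Statistical power section speaks of a change in activity between the arms, which fits either a change from baseline or a difference at follow-up.
- **That the plan risks false positives.** No case examined inflates the type I error; the one faulty model errs on the conservative side.

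What survives is that the section does describe the model structure and does give baseline a role, but only as a comparison of arms. The routes open under its wording differ in power by enough to be worth settling.

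**Conclusion.** This is a free improvement, not a fault that invalidates the analysis. Adjusting for baseline lowers the standard error for steps from about 583 to between 556 and 416 and raises power from 81% to between 85% and 98%, for an assumed r of 0.3 to 0.7 and an assumed ICC of 0.05. At the low end the gain is modest. The powers are normal approximations; with 32 residences actual power will be a little lower (a simulation of the follow-up-only analysis gave 77–78%), but the ordering does not change.

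The arrangement to rule out is stacking baseline and follow-up with residence as the only random effect. It brings type I error to 1% or below at r of 0.5 or 0.7 (about 2.4% at 0.3) and power to 65–74%. The article does not state this model; its wording merely leaves room for it. The calculations concern the linear model for steps, and their size should not be carried over to the logistic models.

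**What to change.** In Data analysis, keep the two-level sentence and add, in substance: each follow-up is analysed separately in the two-level model, with the resident's own baseline value of that outcome as covariate; the primary effect is the difference between arms in average steps per day at end of intervention; the 6-month value is analysed in the same way. Apply this to every secondary outcome with a baseline value.

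If a joint analysis of the occasions is preferred, replace the sentence with three levels (occasion within individual within residence) and take the arm effect at end of intervention from that model.

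The cost is one or two sentences, fixed before outcome data are analysed, with no new measurements. Residents without a valid baseline pedometer record would drop out of the covariate model unless the plan says how they are kept; the joint model can retain them.
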